## Abstract

**Background::**

Oxaliplatin can cause severe peripheral neurotoxicity, which is an important reason for clinical oxaliplatin reduction and cessation of treatment. Oxaliplatin induced peripheral neurotoxicity (OIPN) can cause paresthesia and dysesthesia, even affect the quality life of patients. So far, there are no recognized and effective measures to prevent OIPN. Huangqi Guizhi Wuwu decoction is a classical prescription of ancient Chinese medicine recorded in “the synopsis of the Golden Chamber,” which can be used in the treatment of various neurotoxicity. However, there is a lack of large-scale and high-quality clinical studies on the prevention of OIPN by Huangqi Guizhi Wuwu decoction. The purpose of this study is to evaluate the efficacy and safety of Huangqi Guizhi Wuwu decoction on preventing OIPN.

**Methods/design::**

This study is a randomized, controlled, double-blind, and multicenter clinical trial. Three hundred sixty patients will be randomly assigned into Huangqi Guizhi Wuwu decoction group and Huangqi Guizhi Wuwu decoction mimetic agent group. Patients will receive chemotherapy with FOLFOX of 8 cycles of 3 weeks with Traditional Chinese Medicine (TCM) for 6 months and 1-year follow-up. The primary outcome measure is the differences in the incidence of chronic neurotoxicity of grade 2 and above during and after treatment. The secondary outcome measure is the improvement in other symptoms associated with chemotherapy. Four methods will be used to evaluate the efficacy of neurotoxicity, including oxaliplatin specific toxicity grading standard (Levi classification); CTCAE4.02 version; EORTC QLQ-CIPN20 scale, EORTC QLQ C30 scale, and EORTC QLQ-CR29 scale are used at the same time; Electromyography.

**Discussion::**

This study will provide objective evidences to evaluate the efficacy and safety of Huangqi Guizhi Wuwu Decoction on preventing OIPN.

**Trial registration::**

Clinical Trials.gov (Identifier: NCT04261920).

## Introduction

1

Oxaliplatin is one of the most commonly used chemotherapeutic drugs in clinic. It is effective in ovarian, breast cancer, gastric cancer, pancreatic cancer, non-small cell lung cancer, melanoma, testicular, and lymphoma. More than 70% of patients with gastrointestinal tumors need oxaliplatin chemotherapy. Peripheral neurotoxicity is the main dose-limiting toxicity. About 90% of all patients treated with oxaliplatin have characteristic neurotoxicity.^[1]^ OIPN can be divided into acute neurotoxicity and chronic neurotoxicity (also as known as cumulative neurotoxicity). Transient peripheral neuropathy is the most common acute neurotoxicity in clinic, which is characterized by paresthesia at the end of the limb and hypersensitivity induced or aggravated by cold stimulation.^[2]^ Other acute neurotoxic symptoms include abnormal sensation in the throat, soreness around the mouth, mandibular spasm, and muscle spasm.^[3,4]^ The occurrence and severity of chronic peripheral neurotoxicity depend on the cumulative dose of oxaliplatin. Chronic neurotoxicity usually occurs in patients receiving the dose of oxaliplatin >540 mg/m^2^, characterized by sensory numbness and dullness in the distal limbs, and may affect daily activities, including writing, holding, and other fine movements.^[5]^ The MOSAIC study showed that when patients received the dose of oxaliplatin as 1000 mg/m^2^, 58% of patients developed grade 2 neurotoxicity (affecting daily life) and 18% developed grade 3 neurotoxicity (seriously affecting daily life). The patient recovers very slowly after developing grade 3 of cumulative neurotoxicity. In the MOSAIC study, the median time for patients to recover from grade 3 neurotoxicity to grade 0 was >70 weeks.^[6]^ Therefore, neurotoxicity is an important factor that limits the clinical application of oxaliplatin and affects the quality of life of tumor patients.

Many drugs are also used to try to prevent or reduce OIPN, including acetylcysteine, amifostine, calcium-magnesium mixtures, glutathione, ORG2766, gabapentin, vitamin E, as well as antidepressants and antiepileptic drugs. The 2014 ASCO guidelines^[7]^ reported the results of 48 clinical studies of chemotherapy-related neurotoxicity, only 1 study using duloxetine had positive results, and found that duloxetine reduced chemotherapy-related pain. However, duloxetine is a drug for the treatment of severe depression, with numerous and obvious side effects in cardiovascular, central nervous system, endocrine system, reproductive system, and gastrointestinal system. In 2019, [name] et al^[8]^ conducted a study on GM1 significantly reducing the peripheral neurotoxicity induced by paclitaxel in the treatment of breast cancer, which is the only multicenter double-blind phase III randomized controlled clinical trial that has proved to be effective in preventing neurotoxicity caused by chemotherapy. Therefore, looking for effective drugs to prevent OIPN is still an important problem to be solved.

Huangqi Guizhi Wuwu decoction, listed in Table 1, is recorded in the synopsis of the Golden Chamber, “both yin and yang are weak, the pulse on the upper of cunkou region is faint, the pulse on the middle of chi area is small and tight, the body is numb in external syndrome like wind impediment. It should be treated by Huangqi Guizhi Wuwu Decoction.” According to its clinical manifestation, it belongs to the category of “blood arthralgia” in TCM. According to the records of the Canon of Internal Medicine, its pathogenesis is weakness of Rong Wei, invasion of exogenous pathogenic factor, paralysis of flesh and blood collaterals. The clinical manifestation is the paralysis of the body skin. There are many convergences between the blood arthralgia and the occurrence and development of neurotoxicity caused by oxaliplatin in clinical symptoms. Therefore, Huangqi Guizhi Wuwu decoction is often used to prevent OIPN in clinic.

**Table 1 T1:**
[figure not shown]
Standard formulation of Huangqi Guizhi Wuwu decoction.

## Methods/design

2

### Design

2.1

This study is designed as a randomized, controlled, double-blind, and multicenter trial to evaluate the efficacy and safety of Huangqi Guizhi Wuwu decoction on preventing OIPN. The trial was registered at ClinicalTrials.gov (NCT04261920), and protocol version is version 1.2/20191230. The clinical study will last 36 months and begin from January 2020 to January 2023.

This study will be conducted in 13 clinical centers in China, including Affiliated Hospital of Nanjing University of Chinese Medicine, The First Affiliated Hospital With Nanjing Medical University, Jiangsu Cancer Hospital, Pla Bayi Hospital, The First affiliated Hospital of Soochow University, The Second affiliated Hospital of Soochow University, Suzhou Municipal Hospital, Nantong Cancer Hospital, The first people's Hospital of Changzhou, The second people's Hospital of Changzhou, will recruit 30 patients through posters, Zhangjiagang first people's Hospital, Jiangyin People's Hospital, Pukou branch hospital of Jiangsu Province Hospital. A total of 360 patients will be recruited in all clinical centers. Five phases will be consisted in the study: screening, allocation, intervention, end of intervention, and follow-up. Each patient will give their written informed consent form prior to enrollment. The study's flow chart is shown in Fig. 1.

**Figure 1 F1:**
[figure not shown]
Study flow chart of enrollment, allocation, intervention, and assessment.

### Randomization and allocation

2.2

Block randomization and center-based stratification was carried out in this study. With the help of SAS statistical software, the “random number table of central coding” was generated for a given number of seeds, and the subjects were divided into Huangqi Guizhi Wuwu decoction group and Huangqi Guizhi Wuwu decoction mimetic agent group according to the random number (the ratio of the 2 groups was 1:1).

### Sample size

2.3

In the mosaic study, the incidence of neurotoxicity above grade 2 was 42%. It is assumed that the incidence of neurotoxicity in the test group is 15% lower than that in the control group, 150 cases in each group are required under 80% control. Considering 20% off rate, it is expected 180 cases in each group. Therefore, we will enroll the total sample size of 360 patients for this trial.

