### Statistical analysis

3.9

After the test trial is determined, the statistical professionals shall be responsible for drawing up the statistical analysis plan in consultation with the investigators. The database will be analyzed by SAS 9.4 and will cover actual number of subjects selected, shedding and exclusion of cases, demographics and other baseline characteristics, compliance, efficacy analysis, and safety analysis.

The qualitative data are analyzed by chi-square test, Fisher exact test, Wilcoxon rank sum test, and CMH chi-square test. The quantitative data accord with the normal distribution by *t* test, and do not accord with the normal distribution by Wilcoxon rank sum test and Wilcoxon signed rank sum test. The two-sided test is used in the hypothesis test, and the test statistics and their corresponding *P* values are given, with *P* ≤ .05 as statistically significant and *P* ≤ .01 as highly statistically significant.

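### Section 2.3 adds the 20% loss allowance as 150 × 1.2 instead of 150 / 0.8, so at the planned loss 360 patients give about 77% power, not 80%

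*Protocol article*

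**What the plan says.** The sample-size argument stands in section 2.3 of the protocol article.

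- **Control rate.** Taken from the MOSAIC study, where "the incidence of neurotoxicity above grade 2 was 42" per cent.
- **Effect.** It is assumed that "the incidence of neurotoxicity in the test group is 15% lower than that in the control group".
- **Requirement.** "150 cases in each group are required under 80% control". The last two words can only sensibly mean power.
- **Loss.** "Considering 20% off rate, it is expected 180 cases in each group".
- **Total.** "we will enroll the total sample size of 360 patients for this trial".

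The other settings stand elsewhere. Section 2.2 (Randomization and allocation) says that "the ratio of the 2 groups was 1:1". Section 3.9 (Statistical analysis) says "The two-sided test is used in the hypothesis test" and takes P ≤ .05 as significant. Section 2.3 gives no formula for the power calculation or for the loss allowance.

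**The concern.** The three figures 150, 20% and 180 do not fit together. A loss rate is a fraction of those enrolled. To end with 150 patients, the enrolled number must be divided by the fraction expected to remain; increasing 150 by a fifth does not achieve this. The mismatch can be seen without any assumption about alpha, sidedness or effect size.

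Section 2.3 is the article's only justification of the size of the trial for its primary endpoint. If the loss turns out as planned, the trial will have less power than stated, and a reader weighing a non-significant result would credit it with somewhat more sensitivity than it had.

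**Working it through.** **Inputs.** Control rate 42%, difference 15%, 150 per arm, 80% power and 20% loss are from section 2.3. The 1:1 ratio is from section 2.2. The two-sided test and the 0.05 level are from section 3.9.

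Two readings are needed. I take the 15% as an absolute difference, so 42% versus 27%. A relative reduction (42% versus 35.7%) would need 939 per arm and cannot lie behind 150. I take the test as two-sided, as section 3.9 says. A one-sided 0.05 test would need only 124 per arm, which is further from 150.

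**Step 1: reproduce 150 per arm.** With z = 1.960 and 0.842:

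- Unpooled: n = (1.960 + 0.842)² × (0.42 × 0.58 + 0.27 × 0.73) / 0.15² = 153.7, so 154.
- Pooled, with mean rate 0.345: n = [1.960 × √(2 × 0.345 × 0.655) + 0.842 × √(0.42 × 0.58 + 0.27 × 0.73)]² / 0.15² = 156.5, so 157.

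So 150 reproduces approximately, on the low side. Its power is 78.3% (pooled) or 79.0% (unpooled).

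**Step 2: reproduce 180 per arm.**

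- 150 × 1.2 = 180, the stated figure.
- 150 / (1 − 0.20) = 187.5, so 188 per arm and 376 in total.
- Shortfall: 376 − 360 = 16 patients.
- Left after 20% loss from 180: 180 × 0.80 = 144 per arm.
- Largest loss at which 180 still leaves 150: 1 − 150/180 = 16.7%.

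**Step 3: power for 42% versus 27%, two-sided 0.05.**

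Pooled power = Φ{[0.15 − 1.960 × √(2 × 0.345 × 0.655 / n)] / √[(0.42 × 0.58 + 0.27 × 0.73) / n]}. For n = 144 this is Φ{(0.15 − 1.960 × 0.05602) / 0.05532} = Φ(0.727) = 76.6%. The unpooled version is Φ(0.15 / 0.05532 − 1.960) = Φ(0.751) = 77.4%.

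| Evaluable per arm | Pooled | Unpooled | Exact enumeration, uncorrected chi-square |
|---|---|---|---|
| 144 (20% loss) | 76.6% | 77.4% | 77.1% |
| 150 (16.7% loss) | 78.3% | 79.0% | 78.2% |
| 180 (no loss) | 85.2% | 85.8% | 85.5% |

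**Step 4: where 80% is lost.** Power reaches 80% at 154 (unpooled) to 157 (pooled) per arm. From 180, that corresponds to a loss of 1 − 154/180 = 14.4% or 1 − 157/180 = 12.8%.

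**Step 5: detectable difference.** With 144 per arm and a 42% control rate, 80% power corresponds to a difference of 15.5 points (unpooled) to 15.6 points (pooled), against the 15.0 assumed.

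**The case against.** The strongest objection is that 360 patients can deliver 80% power. If all 180 per arm contribute to the primary analysis, power is about 85%, and it stays at or above 80% while loss is below roughly 13–14%. The article names no analysis set; that may be in the statistical analysis plan. The primary outcome covers the period during and after treatment, and section 3.3 has visits between cycles, so some patients who leave late may already have a recorded outcome. This stands. A reader might infer that 360 is too few in any event, and the document does not support that. The figure of 144 is what the protocol's own planning assumption implies, not a known analysis size. The objection does not rescue the calculation, though, because section 2.3 itself treats the 20% as patients to be made up for.

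A second objection is that 150 per arm is not an error of weight. This also stands: the gap to 154–157 is within what choice of formula and rounding produce, and the article gives no formula. A reader might also apply a continuity correction, which asks for 170 per arm, but section 3.9 specifies none, so that figure has no basis in the plan.

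Third, the effect is small. The multiplication slip alone costs about 1.7 points of power (78.3% to 76.6%, pooled); the rest of the gap to 80% was there at 150. The control rate is also uncertain: the Introduction reports 58% grade 2 and 18% grade 3 neurotoxicity from the same study that section 2.3 cites for 42%. With 144 per arm and the same 15-point difference, pooled power would be 72.3% at a control rate of 58%, and, taking two lower rates purely for illustration, 79.3% at 38% and 81.7% at 35%. This limits how precisely the power can be stated and bears on severity. It does not explain why 150, 20% and 180 disagree.

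Finally, neither condensation into an article nor deferral to an analysis plan answers the point. The calculation is given, and it is given wrongly.

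**Conclusion.** The loss allowance in section 2.3 is wrong as written. On the protocol's own figures, 150 evaluable per arm after 20% loss needs 188 per arm (376 in total); 180 per arm leaves 144. At that loss, power for 42% versus 27% is 76.6–77.4% depending on method, about 3 points below the stated 80%.

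The 144 and the 188 rest only on the stated 150 and 20%. The power figure also rests on three readings: a two-sided 0.05 test, an absolute 15-point difference from 42%, and lost patients contributing nothing to the primary analysis. It must therefore be stated as power at the planned 20% loss. An unconditional claim that the trial lacks 80% power would go too far.

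The slight shortness of 150 is a footnote to the same paragraph. Severity: should-fix. The error is certain, but a gap of about 3 points does not call the design into question.

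**What to change.** Keep 360 patients and rewrite the paragraph in section 2.3 so that its numbers agree. Either version would do:

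- *With 180 patients per arm and 20% loss, 144 per arm are evaluable. This gives about 77% power for 42% versus 27% at two-sided alpha 0.05; 80% power corresponds to a difference of about 15.5–15.6 percentage points.*
- *With 180 patients per arm, 150 per arm are retained provided that loss does not exceed 16.7%. This gives about 78% power for 42% versus 27% at two-sided alpha 0.05.*

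Both state the alpha, the sidedness and the absolute scale of the difference, which section 2.3 now leaves to be inferred. The cost is one rewritten paragraph and a slightly less favourable stated power. No patients are added, and neither the design nor the analysis changes.

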### Eligibility criteria

2.4

Inclusion criteria:

(I)Subject with colorectal cancer diagnosed by histopathological examination; subject after radical resection of colorectal cancer confirmed by histopathological examination, staged as high-risk II stage (according to CSCO guidelines for diagnosis and treatment of colorectal cancer) or III stage, IV stage (metastatic lesions have been radical resection);(II)Subject who is suitable for receiving oxaliplatin plus capecitabine regimen as adjuvant chemotherapy for 6 months, the cumulative dose of oxaliplatin is expected to exceed 520 mg/m^2^ at least;(III)Subject is between 18 and 75 years of age, men or women;(IV)ECOG score ranges from 0 to 1(V)Seven days before treatment, the functions of major organs (heart, liver, kidney, bone marrow) meet the following criteria:Standard of blood routine examination (without blood transfusion within 14 days)i.Hemoglobin (HB) ≥90 g/L;ii.Absolute neutrophil count (ANC) ≥1.5 × 109/L;iii.Platelet (PLT) ≥80 × 109/L.Biochemical examination should meet the following standards:i.Total bilirubin (TBIL) ≤1.5 times upper normal limit (ULN);ii.Alanine aminotransferase (ALT) and aspartate aminotransferase (AST) ≤2.5 times ULN;iii.Serum creatinine (Cr) ≤1.5 times ULN or creatinine clearance (CCr) ≥60 mL/min;(VI)Expected survival time ≥12 months;(VII)For subjects who have used other chemotherapeutic drugs in the past, they need to go through a clearance period of at least 4 weeks before entering this trial.(VIII)The subjects who have signed the informed consent form.

Exclusion criteria:

(I)Subject had original nervous system diseases, including peripheral neuropathy and central neuropathy;(II)Subject who are allergic to oxaliplatin or the ingredients of this traditional Chinese medicine;(III)Clinical symptoms of subject with severe damp-heat syndrome of colorectal cancer include: dry mouth, bitter taste in the mouth, sticky sensation in mouth, yellow urine, dry stool, red tongue with yellow, thick and greasy fur;(IV)Subject had neurological disease caused by electrolyte disorders or diabetes;(V)Subject had symptoms of nerve compression caused by various causes;(VI)At the same time, subject received other neuroprotective therapy, including nerve growth factor, vitamin B and calcium-magnesium mixture;(VII)Subject was treated with oxaliplatin for chemotherapy before;(VIII)Subject needed radiotherapy within half a year after operation;(IX)Pregnant or lactation period women;(X)Subject had cognitive impairment or psychosis;(XI)Other subjects the investigator considers unsuitable for inclusion.

## Interventions

3

### Huangqi Guizhi Wuwu decoction granule group

3.1

Participants in the Huangqi Guizhi Wuwu decoction granule group will be treated with Huangqi Guizhi Wuwu decoction.

Participants will have been taking Huangqi Guizhi Wuwu decoction during adjuvant chemotherapy with XELOX regimen for 6 months (3 weeks per cycle for 4 cycles). Huangqi Guizhi Wuwu decoction will be taken twice a day, infused with warm water, 1 hour after lunch and dinner. One course of treatment will take 21 days. Participants will be contacted by telephone every one cycle and queried regarding adherence to study agents, illnesses, medication, and supplement use. The assessment that needs to be performed at visit is listed in Table 2.

**Table 2 T2:**
[figure not shown]
Study phases schedule for enrollment, intervention, and assessment.

### Huangqi Guizhi Wuwu decoction mimetic agent group

3.2

Huangqi Guizhi Wuwu decoction mimetic agent group's treatment and measurements are in accordance with the Huangqi Guizhi Wuwu decoction group.

### Treatment cycles

3.3

Six months treatment period will be planned in 8 cycles of 3 weeks. Between each cycle we will return visit participants to evaluate the efficacy of neurotoxicity. Chronic neurotoxicity can only be evaluated after chemotherapy, once every 2 months and followed up for 1 year.

### Intervention drugs and blinding

3.4

Intervention drugs are Huangqi Guizhi Wuwu decoction and Huangqi Guizhi Wuwu decoction mimetic agent, which are provided by Tianjiang Pharmaceutical Group Co. Ltd., Wuxi, China. The size, shape, color, taste, package, and Lot number between Huangqi Guizhi Wuwu decoction and the mimetic agent is same.

The work of setting up blindness is completed by statisticians of Jiangsu Famous Medical Technology Co., Ltd. and is divided into 2 levels. The first level of blindness is the blindness of experimental drugs, which are unified packaging. The secondary blindness is the number of the packaging box of experimental drugs.

Only when it is really necessary to break the code in case of emergency, the researcher shall consult the person in charge of the center. With the signature of the person in charge of the center, the emergency blind letter can be opened and recorded, and the clinical research unit shall be notified within 24 hours after the blindness is broken.

### Drug combination

3.5

During this study, participants with grade 2 or more neurotoxicity should be allowed to receive necessary drug treatment and their use must be recorded in detail in the CRF. However, following medication should be prohibited before the termination of the trial: antiepileptic drugs, such as acarbazepine, gabapentin; calcium-magnesium mixture, such as calcium gluconate, magnesium sulfate; vitamins, such as vitamin B, vitamin E; nerve growth factor; amifostine; other traditional Chinese medicine.

### Outcome evaluation

3.6

#### Primary outcome

3.6.1

The primary outcome measure of this study is the differences in the incidence of chronic neurotoxicity of grade 2 and above during and after treatment.

#### Secondary outcome

3.6.2

The secondary outcome measure is difference in the incidence of acute neurotoxicity; time of occurrence of chronic toxicity to grade 2 and 3; incidence and severity of main symptoms; recovery time of grade 2 and 3 neurotoxicity; cumulative dose of oxaliplatin and the proportion of patients who stop using oxaliplatin because of neurotoxicity; incidence of myelosuppression and incidence of nausea, vomiting, diarrhea, and hand-foot syndrome.

### Safety evaluation

3.7

Up to date, there are no reports of adverse reactions in clinical application of Huangqi Guizhi Wuwu decoction. However, participants may have toxic reactions of hematopoiesis, digestive system, and nervous system when using oxaliplatin, and toxic reactions such as digestive system and skin may occur when using capecitabine. To monitor the adverse reactions when using chemotherapy, some check must be taken including routine examination, urine routine examination, liver function test, renal function test, bone marrow function test (blood routine), serum pregnancy test (women only), electromyography.

All adverse events, including toxicity and side effects such as toxic reactions of hematopoietic system, gastrointestinal system, and nervous system, should be recorded in the CRF in detail. When an adverse event occurs, the investigators should decide whether to stop the trial according to the severity, and the corresponding treatment should be given in time according to the patient's condition. In case of serious adverse events, immediate measures should be taken to protect the safety of the patients. Adverse events should be reported to each hospital.

